### Recruitment and sample selection

Participants were recruited nationwide, with additional local efforts from flyers and clinician referrals within the VAPORHCS, OHSU, and surrounding Portland-Metro area (Fig 2). The most successful recruitment methods included repositories, referrals, internet-based advertisements, flyers, and radio ads, all described in more detail below. Recruitment began 6/1/2019 and remains ongoing.

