#### Fidelity adherence monitoring

Adherence to both MBLT and sham was tracked and consistently monitored in several ways. First, we called participants at the onset of initiating their intervention, as well as weekly thereafter to address any questions and promote their adherence by way of addressing any challenges they had encountered. Second, participants manually recorded their engagement with their device (time and duration) as part of their daily sleep-diary. Third, we utilized a combination of actigraphy and luxometer data (generated and collected by the Actiwatch-2 as well as a HOBO Pendant MX Temperature/Light Data Logger affixed to the LightPad) to objectively track MBLT adherence. Luxometer data via the HOBO and/or actiwatch provided evidence of device usage, and activity counts via the actiwatch provided an estimate of movement such that the combination of low activity counts (i.e., suggesting being sedentary) and evidence for device usage, suggested protocol adherence. This did not preclude the possibility that participants turn the LightPad on and either have it incorrectly placed (facing away from them), or simply remain sedentary in a different room, but the combination of these metrics provided a best approximation while minimizing participant burden.

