#### Self-report, actigraphy, and sleep diary

Potential changes in sleep were further evaluated via other validated self-report measures (e.g., Epworth Sleepiness Scale, ESS [56]; Functional Outcomes of Sleep Questionnaire-10, FOSQ-10 [57]; and the Sleep Hygiene Index, SHI [58]), and objective metrics derived from participants’ sleep diary and wrist-based actigraphy (Philips Respironics, Bend, OR, USA). Philips Actigraphy devices use a solid-state, piezoelectric, monoaxial accelerometer to measure activity and silicon photodiodes to measure photopic light (5–100,000 lux; 400–900 nm), with data sampled at 32 Hz and aggregated into 2-minute bins. Philips Actiware (v 6.3.0) was used to process and analyze these data relying first on the automated algorithmic detection of rest-active periods, with further refinement based on *a priori* defined outcomes collected in the sleep diary. For example, participants were queried whether their sleep was unusually disrupted (ranging from being ill to falling asleep or being awoken at unusual times due to things outside of their control), and if so, this 24-hour period was excluded from analysis. Participants were directed to wear the watch on their non-dominant wrist and to keep clothing from covering the light sensor as much as possible. Daily sleep diaries were collected using the TWILIO^™^ platform, which directly integrated with our HIPAA-compliant secure REDCap database. Participants were prompted in the morning via Short Message Service (SMS) text format. The first prompt was at 8:00 AM in participants local time, with reminders sent at 10:00 AM and 12:00 PM if no response had been entered. If participants did not respond within that 24-hour period, earlier prompts expired ensuring all data is collected within 24 hours. Sleep diary metrics included self-reported time in bed/asleep, time out of bed/awake, number of awakenings during the night, and (during the intervention period) device usage.

The primary comparison across timepoints was pre- vs post-intervention. Only self-reported sleep symptoms were evaluated at the follow-up time point as daily diaries and actigraphy were not continued during the follow-up period.

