To analyze treatment effect over time (pre-, post-, and follow-up), we will implement mixed effects models (either linear or gamma, pending data normality) for each outcome measure under consideration. This flexible approach allows us to examine the change pattern and accounts for within-subject correlations over multiple time points. This approach also maximizes our observed data by way of accommodating missing data at random. The main effects in each model will be the treatment and time effects, including a treatment-by-time interaction effect. The models may be adjusted for possible confounders, such as age, sex, fidelity adherence (lux/min), geographic location/seasonality, sleep hygiene, and depression. With a significant omnibus test suggesting the global null hypothesis is rejected, a Bonferroni or Tukey HSD post-hoc analysis will be performed.

Within the MBLT group we will use linear regression to analyze the relationship (goodness of fit; r^2^) between average morning lux exposure (quantified as lux/min by the Actiwatch) and the degree of change in dependent variables (e.g., sleep efficiency, self-reported sleep quality, neurocognitive outcomes, and other self-reported functional outcomes) between pre- and post-treatment. Within select patient outcome questionnaires, we will perform Pearson correlational analyses to determine how each patient outcome questionnaire varies together (Pearson correlation coefficient; r). Actigraphy variables will be compared to appropriate self-report and objective outcomes in the form of discrete time-period averages (i.e., 3–5 consecutive representative nights within the last ~7 days of both the baseline and intervention periods). Secondarily, if permissible, we will implement analyses based on a 3-day moving average, leveraging the unique frequency of data acquisition inherent to 24/7 actigraphy.

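### Wrist-measured morning lux mixes lamp light with daylight, so the within-MBLT regression cannot by itself attribute an association to the lamp and will tend to understate a true lamp dose-response

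*Protocol article*

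**What the plan says.** The Statistical analyses section fixes the arm and the method: "Within the MBLT group we will use linear regression to analyze the relationship (goodness of fit; r^2". The exposure it names is "average morning lux exposure (quantified as lux/min by the Actiwatch", with pre-to-post change in sleep, cognitive and functional measures as the outcome. No covariate is named for this regression.

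The preceding paragraph, on the mixed models, says: "The models may be adjusted for possible confounders, such as age, sex, fidelity adherence (lux/min), geographic location/seasonality, sleep hygiene, and depression". That adjustment is optional and belongs to the mixed models. It also shows that the plan treats lux/min as a measure of adherence to treatment.

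On the sensor, the section on self-report, actigraphy and sleep diary describes "silicon photodiodes to measure photopic light (5–100,000 lux; 400–900 nm", worn on the wrist. The Fidelity adherence monitoring section describes a second, lamp-mounted device, "a HOBO Pendant MX Temperature/Light Data Logger affixed to the LightPad", which is used for adherence and not named in the regression.

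On spread of season and place, Recruitment and sample selection describes nationwide recruitment and states "Recruitment began 6/1/2019 and remains ongoing".

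**The concern.** The Actiwatch does not distinguish light sources: sun, windows and time outdoors register alongside the lamp. Restricting the regression to the MBLT arm, and calling lux/min fidelity adherence, invites readers to take the slope as a treatment dose-response. Yet part of the spread in morning lux between participants comes from when in the year they took part, where they live and whether they go outside early. Randomisation balances these factors in expectation between arms, but it does nothing for a regression inside one arm.

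Two things are at stake. A positive slope could be reported as biological support for MBLT when the lamp did not produce it. Conversely, a real lamp dose-response could be diluted and reported as weak or absent.

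**Working it through.** The documents give no power or precision figure for this regression, so there is no stated figure to reproduce.

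**1. Attenuation.** Let L be lamp light, D the daylight part of morning lux, independent of L, and k = var(D)/var(L). If only the lamp acts, change = b·L + error, and the regressor is X = L + D. The expected slope is then b·var(L)/[var(L) + var(D)] = b/(1 + k). With an assumed b of 0.30:

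| k | expected slope | simulated slope (n = 69, 3,000 replicates) | loss |
|---|---|---|---|
| 0.5 | 0.30/1.5 = 0.200 | 0.195 | 33% |
| 1 | 0.30/2 = 0.150 | 0.150 | 50% |
| 2 | 0.30/3 = 0.100 | 0.099 | 67% |

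**2. What k means in lux.** Document inputs are 10,000 lux at the eye (Introduction), 60 minutes within a 120-minute window (Interventions), and objective use of 22.4 ± 7.7 of 28 days in MBLT participants with mTBI (Table 3). If the wrist reads the same as the eye (an assumption), the lamp part of a 120-minute morning average has mean 10,000 × 60/120 × 22.4/28 = 4,000 lux and SD 10,000 × 60/120 × 7.7/28 = 1,375 lux. Then k = 0.5 corresponds to a daylight SD of 1,375 × √0.5 ≈ 972 lux, and k = 2 to 1,375 × √2 ≈ 1,945 lux.

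The lamp share of variance is 1,375²/(1,375² + SD²). With an assumed true lamp correlation of 0.4, the observed correlation is 0.4 × √share. Power is by Fisher z at the planned n = 80:

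| assumed daylight SD (lux) | lamp share | observed r | power |
|---|---|---|---|
| 500 | 0.88 | 0.38 | 0.93 |
| 1,000 | 0.65 | 0.32 | 0.84 |
| 2,000 | 0.32 | 0.23 | 0.53 |
| 4,000 | 0.11 | 0.13 | 0.21 |

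An error-free lamp-only exposure would keep r = 0.4, with power 0.96. If the wrist receives half the eye lux, the lamp share runs from 0.65 to 0.03 over the same daylight SDs.

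**3. False attribution.** Split daylight into a stable part S, present in both periods, and a shift Δ from baseline to intervention. If daylight affects the level of an outcome with coefficient g, S cancels in the change score: change = b·L + g·Δ + error. The planned regressor is X = L + S + Δ. With b = 0 and independent parts, the slope is g·var(Δ)/[var(L) + var(S) + var(Δ)]. It is driven by the shift and not by stable latitude or habit.

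Some shift is plausible. The middle of the 14-day baseline is day 7, and the middle of a 28-day intervention following directly is day 14 + 14 = 28, so the two are at least 21 days apart. Day length lengthens or shortens over that gap depending on the time of year. The documents give no value for var(Δ) or g, so no rate can be computed.

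**The case against.** The strongest reply has five parts.

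- **The plan says morning lux exposure, not lamp dose.** As a description of total morning light the regression is valid, and if daylight helps sleep a positive slope is a true association. This stands, and it is why relabelling is an acceptable minimum. The adherence label and the restriction to MBLT still point readers towards dose.
- **The outcome is a change.** A reader might infer that the regression would often be significant with no lamp effect. Placing a 0.3 SD daylight effect directly on the change score does give 27% to 49% significant results at n = 69 for k from 0.5 to 2. The documents do not support that premise, because stable latitude and habits act in both periods and largely cancel. Those percentages should not be used.
- **The lamp may dominate.** With a daylight SD of 500 to 1,000 lux the lamp share is 0.88 to 0.65. In addition, 47 of the 69 MBLT participants in Table 1 (30 + 17; 68%) live in Pacific time, and latitude is not reported. This stands: the attenuation could be small.
- **The HOBO logger has its own error.** The protocol concedes that a lamp may be on while facing away or while the participant is elsewhere, and lux received depends on distance. Logs may also be incomplete. This stands, so HOBO data suit a sensitivity analysis better than the main exposure.
- **Covariates can be left to the SAP.** This is fair as to detail, but the article itself fixes the exposure.

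**Conclusion.** The concern holds in limited form. The exposure as fixed cannot separate lamp light from daylight, so this regression alone cannot attribute an association to the lamp. A true lamp slope is attenuated by 33% to 67% if daylight variance is 0.5 to 2 times lamp variance and the two are independent. That ratio is assumed, and the loss would be smaller if daylight varied little. False attribution is possible mainly through shifts in daylight or outdoor habits between periods, and its size is not established.

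A reader might infer that the regression can show nothing about the lamp, or that the trial's efficacy conclusion is at risk. Neither follows: wrist lux does contain the lamp signal, and the randomised MBLT-versus-sham comparison of ISI does not use this exposure. This is a low-cost improvement to a supporting analysis.

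**What to change.** Amend the wording of this regression before efficacy results are examined; the Results section says outcome analyses have not yet been explored.

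1. Use as exposure each person's intervention-period minus baseline-period Actiwatch morning lux, or keep intervention-period lux and add baseline morning lux as a covariate. This addresses the stable daylight part.
2. Add season, or day length from calendar date and residence. Baseline subtraction leaves the shift Δ in the exposure, so this term is still needed.
3. Report the identical regression in the sham arm, which wears the same watch without a lamp, as a negative control. Use it to inform interpretation and not as a significance gate: at the planned n = 40, a correlation reaches p < 0.05 only above 2.024/√(2.024² + 38) ≈ 0.31, so a non-significant sham slope would not exclude a daylight contribution.
4. Repeat the analysis with HOBO-confirmed lamp sessions as a sensitivity analysis where logs exist.
5. If none of this is adopted, label the exposure total morning light, not therapy dose.

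The cost is analysis-plan wording and some extra programming. The data streams are already in the protocol, although collection was still under way at publication. The downsides are one or two degrees of freedom, added measurement noise from subtracting a baseline of at most 14 days, and possibly a lower r².

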### Randomization, allocation, and masking

After receiving informed consent, HIPAA authorization, and completing the 2-week baseline period, participants were randomized in a 2:1 allocation ratio, active intervention to sham and recorded according to the Consolidated Standards of Reporting Trials (CONSORT; Fig 3). Although participant-masked (i.e., investigators know all negative ion generators are inactive), study arms were verbally described to participants in a “pseudo” double-masked fashion, as before [28]. Specifically, all participants were informed that 50% of both study arm devices were inactive and neither they, nor us, knew whether they receive an active device until completion. After the study had been completed, a team member then disclosed to all participants their randomization status, and provided the scientific rationale necessitating the use of deception. Additionally, study investigators described these study arms as “devices”, rather than “therapies”, throughout the protocol, which was technically accurate and precluded unmasking.

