**Secondary Outcomes**				
Full questionnaire battery				
Pre-intervention	47 (100%)	22 (100%)	24 (100%)	11 (100%)
Post-intervention	43 (91%)	17 (77%)	20 (83%)	11 (100%)
Cognitive Assessment				
Pre-intervention	47 (100%)	22 (100%)	24 (100%)	11 (100%)
Post-intervention	45 (96%)	22 (100%)	23 (96%)	11 (100%)
DLMO				
Pre-intervention	40 (85%)	18 (82%)	21 (88%)	10 (91%)
Post-intervention	38 (81%)	19 (86%)	20 (83%)	11 (100%)
Biospecimen sample				
Pre-intervention	41 (87%)	19 (86%)	21 (88%)	9 (82%)
Post-intervention	40 (85%)	17 (77%)	20 (83%)	6 (55%)

Data are presented as mean ± standard deviation, or *n* (%). Pre-intervention assessments span a maximum of 14 days. Post-intervention assessments and device adherence spans a maximum of 28 days. DLMO, dim light melatonin onset.

With respect to participant retention, of the *n* = 140 participants who have provided informed consent, *n* = 24 have withdrawn or been terminated (Fig 3), and therefore *n* = 116 (83%) have been retained. At the time of this interim analysis, complete pre- and post-intervention data has been recorded in n = 104 participants and therefore the remaining n = 12 participants have been randomized/allocated and are currently ongoing.

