**Fig 5 pone.0305305.g005:**
[figure not shown]
Intervention adherence. Device use (self-report and objective), sleep diary and actigraphy data collected during intervention (over 28 days) in the active (**A**) and sham (**B**) conditions. The dashed line indicates the 70% threshold for adherence (20 days). Each data point represents a single participant and corresponds to the number of days they have complete data.

With respect to our primary outcome (ISI score), >95% of participants in both study arms have provided both pre- and post-intervention data. Supplemental sleep related outcomes included wrist-based actigraphy and sleep diary entries, the completeness for both of which was expressed in terms of the number of days with full/usable data (i.e., out of a maximum of 14 days for the baseline period and out of a maximum of 28 days for the intervention period). For both actigraphy and sleep diaries, we reported >83% of participants have complete data, defined as a minimum of 10 days of data recorded at baseline (Fig 4A and 4B) and 20 days of data recorded during the intervention period (Fig 5A and 5B), reflecting >70% of days for both periods.

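### The actigraphy summary averages 3–5 nights with no objective rule for choosing them, which leaves room for selection and omits valid nights inside the plan's own 7-day window

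*Protocol article*

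**What the plan says.** The Statistical analyses section of the protocol article gives one unconditional summary for actigraphy: "Actigraphy variables will be compared to appropriate self-report and objective outcomes in the form of discrete time-period averages", which it specifies as "3–5 consecutive representative nights within the last ~7 days of both the baseline and intervention periods". A further analysis is conditional: "Secondarily, if permissible, we will implement analyses based on a 3-day moving average".

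The section on self-report, actigraphy and sleep diary describes the processing. Rest and activity periods are detected by algorithm first and then refined with diary items defined in advance. Where the participant reports an unusually disrupted night, "this 24-hour period was excluded from analysis".

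On masking, the section on randomization, allocation and masking says the trial is participant-masked and that "investigators know all negative ion generators are inactive". The Shipping section has study coordinators download the watch recordings. The article does not say who selects the nights or whether that person is masked.

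On status, the abstract lists actigraphy among the primary sleep outcomes. The Outcomes section keeps the ISI as primary, and the power calculation rests on it.

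On the data available, the Table 3 footnote says "Pre-intervention assessments span a maximum of 14 days" and "Post-intervention assessments and device adherence spans a maximum of 28 days". The Results section calls actigraphy complete at 10 of 14 baseline days ("defined as a minimum of 10 days of data recorded at baseline") and 20 of 28 intervention days.

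**The concern.** The rule leaves four things open: how many nights (3, 4 or 5), where the run starts, what makes a night representative, and how far back the window of about seven days reaches. *Representative* cannot simply mean undisturbed, because disrupted nights have already gone under the diary rule. It is a second filter with no definition. This is a rule that the article states and fixes badly, not a detail left to an unseen analysis plan.

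Two things are at stake. First, actigraphy is in effect the trial's only objective measure of sleep: the ISI and the diary are self-reported, and dim light melatonin onset measures circadian timing. A choice of nights with no rule, in a trial that masks participants only, weakens the measure a reader would use to corroborate the ISI. Second, a mean of 3–5 nights is noisier than a mean of all valid nights in the same final week. That loss occurs even if the choice is entirely fair.

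**Working it through.** The article states no power or precision figure for actigraphy, so there is none to reproduce.

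**1. Room for choice.** In 7 valid nights there are 7 − k + 1 consecutive runs of length k:
- k = 3: 5 runs; k = 4: 4 runs; k = 5: 3 runs.
- Total 5 + 4 + 3 = 12 per period, hence 12 × 12 = 144 pre/post pairs per participant.

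A missing or excluded night lowers the count.

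**2. Nights left out of this summary.** Unused share = 1 − k / nights available, for k = 5 and k = 3:
- of 14 baseline nights: 64% to 79%
- of 28 intervention nights: 82% to 89%
- of the last 7 nights: 29% to 57%

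Table 3 gives group means of 11.2–13.5 actigraphy days at baseline and 23.5–25.6 during the intervention. As a share of the maximum this is 80–97% and 84–91%, so about 6 valid nights in 7 (86%) is a realistic figure.

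**3. Precision of the pre–post change.** Take the total single-night variance as 1, the single-night ICC as ρ, the variance of true change as tv, and nights as independent within a person. With k₁ baseline and k₂ intervention nights:

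Var(change) = tv + (1 − ρ)(1/k₁ + 1/k₂)

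Neither ρ nor tv is in the article. The assumed ranges are ρ = 0.3–0.5 and tv = 0.1–0.2. The proportional gain is largest at ρ = 0.3, tv = 0.1 and smallest at ρ = 0.5, tv = 0.2.

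| Nights (pre+post) | ρ = 0.3, tv = 0.1 | ρ = 0.5, tv = 0.2 |
|---|---|---|
| 3+3 | 0.1 + 0.7 × 0.667 = 0.567 | 0.2 + 0.5 × 0.667 = 0.533 |
| 4+4 | 0.1 + 0.7 × 0.500 = 0.450 | 0.2 + 0.5 × 0.500 = 0.450 |
| 5+5 | 0.1 + 0.7 × 0.400 = 0.380 | 0.2 + 0.5 × 0.400 = 0.400 |
| 6+6 | 0.1 + 0.7 × 0.333 = 0.333 | 0.2 + 0.5 × 0.333 = 0.367 |
| 7+7 | 0.1 + 0.7 × 0.286 = 0.300 | 0.2 + 0.5 × 0.286 = 0.343 |

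Reductions in variance:
- 4+4 to 7+7: 1 − 0.300/0.450 = 33%; 1 − 0.343/0.450 = 24%
- 5+5 to 6+6: 1 − 0.333/0.380 = 12%; 1 − 0.367/0.400 = 8%
- 3+3 to 6+6: 1 − 0.333/0.567 = 41%; 1 − 0.367/0.533 = 31%

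In the middle of the range (ρ = 0.4, tv = 0.2) the variance is 0.500 for 4+4 and 0.371 for 7+7, a reduction of 26%.

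**The case against.** **Who picks.** A reader might infer that unmasked staff hand-pick the nights. The article does not say so. It says that investigators know the ion generators are inactive and that coordinators download the watches. It is silent on who selects the nights, and masked or programmed selection could be described in the full protocol. What stands is that the published rule has no objective criterion and no stated masked selector.

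**Scope.** The sentence follows one on correlations between questionnaires and is worded as a comparison of actigraphy with other outcomes. The mixed model for the treatment effect is set out in the preceding paragraph without any night window. This is fair. But the sentence names both periods, and no other unconditional actigraphy summary is given for the treatment comparison, so applying it there is the natural reading, though not an explicit one.

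**Safeguards.** Automated detection comes first, refinement follows diary items set in advance, the nights must be consecutive and late in the period, and a 3-day moving average may draw on more nights. These limit discretion over sleep–wake scoring and narrow the choice of run, but they do not settle which run is used. The moving average is secondary and conditional.

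**Bias.** Always taking the most favourable run would shift a period mean by about 0.51, 0.32 or 0.19 night-level SDs for runs of 3, 4 or 5 nights. A reader might take this as the expected bias. It is a worst case with independent nights, and it biases the comparison of arms only if picking differs by arm. In a simulated null trial with runs picked at random, type I error stayed near 5%. Nothing in the article shows differential picking.

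**Diary exclusion.** This is an advance rule based on masked participants' own reports, not staff selection, and it should stay.

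**A longer window.** Using 12 baseline and the last 14 intervention nights instead of 4+4 would lower the variance by 38–54% under the same assumptions. But it averages in earlier treatment nights and so changes what is estimated. It is not a like-for-like gain.

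**Conclusion.** The point holds in a limited form. As published, the rule does not determine which nights enter the actigraphy average: 12 runs per period are admissible when seven nights are valid. The trial masks participants only, and the article does not state whether the selector is masked. That is an opening for selection, not evidence that selection took place.

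The loss of precision does not depend on who picks. It runs from about 8–12% of the change variance (5 nights used when 6 are valid) to about 31–41% (3 used when 6 are valid), and is 24–33% for 4 against a full 7. In standard-error terms these are roughly 4–6%, 17–23% and 13–18%. All rest on the assumed ICC and change variance and on independent nights.

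The point concerns an outcome that the abstract lists as primary but that the trial is not powered on. The ISI result is not affected.

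**What to change.** Before outcomes are analysed, replace the 3–5 night rule with a programmed one:

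- **Main definition.** Each actigraphy outcome is the mean of all valid nights in the last 7 days of the baseline period and the last 7 days of the intervention period, with no selection.
- **Minimum count.** Fix the number of valid nights required in each window. For example, 5 of 7 (71%) would match the article's own 70% completeness threshold. Windows below the minimum are treated as missing under the plan's missing-data rules.
- **Diary exclusion.** Keep it in the main analysis, and report a sensitivity analysis that includes the flagged nights.
- **Longer window.** All baseline nights and the last 14 intervention nights can serve as a further sensitivity analysis, labelled as covering earlier treatment nights.
- **Clarifications.** Say that this definition feeds the treatment comparison, or state the other summary that does. Say who carries out any remaining manual scoring and whether that person is masked to arm, including to the watch's light channel, which may reveal it.

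The cost is a scripting change on recordings the trial already collects, with no burden on participants. The Results section says that formal outcome analyses had not been carried out, so at that stage the change could still be made without knowledge of the results.
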